### Statistical Methods

Full analysis set (FAS) and per-protocol set (PPS) will be both used for statistical analysis in this study. In FAS, for missing outcome data, multiple imputations will be used o. For continuous data, they will be represented as mean ± standard deviation and frequency or percentage for categorical data. Statistics will be analyzed with SPSS 22.0 (SPSS Inc., Chicago, IL). For primary outcomes, the chi-square test will be applied to analyze the POUR incidence. For secondary outcomes, the comparison of UTI incidence, AEs, and catheterization rate will be analyzed by the chi-square test; the independent-sample *t*-test or Mann–Whitney *U* test for intergroup comparison will be used for the time to first urination and the length of hospitalization after considering the normality and homogeneity. The dropout rates will be analyzed by the chi-square test, and the impact of the dropout rate will be further analyzed by comparing dropout reasons, characteristics of dropout cases between groups, and the results using intention-to-treat and per protocol. Statistical testing is two-sided, and *p* < 0.05 is considered statistically significant.

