### Sample Size

The sample size estimate is based on a two-arm normal design. The ratio of the two groups is set as 1:1, and the significance level of the test is targeted at 0.05, with the power achieved to detect a difference set as 0.8. According to a previous literature report, the incidence of POUR after taking tamsulosin hydrochloride was 28.1% (21). In our preliminary experiment, the incidence of POUR after moxibustion therapy is 15%. Considering the dropout rate of no more than 20%, 180 cases will be required for each group.

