### Treatment Group

Moxibustion therapy will be used 1, 10, and 24 h after operation. Moxibustion members who have more than 1-year experience in mild moxibustion will be retrained for standard management of the study. The moxa rolls for moxibustion are produced by Nanyang Chinese Medicine Airong Co. Ltd., in 18 × 200 mm. Points of Qihai (CV 6), Zhongji (CV 5), Guanyuan (CV 4), and bilateral Sanyinjiao (SP 6) will be selected for moxibustion.

In the procedure of moxibustion, the patient takes the supine position with the abdominal skin exposed; the moxibustion members lit the moxa rolls and put them 2–3 cm above the five points for 20 min. When the patients cannot urinate with urgent micturition desire within 24 h after the operation, catheterization will be performed.

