### Control Group

Tamsulosin hydrochloride [0.2 mg, Astellas Pharmaceutical Co., Ltd., China] will be given once to patients 1, 10, and 24 h after operation. When the patients could not urinate with urgent micturition desire within 24 h after the operation, catheterization will be performed (Table 1).

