### Outcome Variables

#### Primary Outcomes

*POUR incidence*: POUR is deﬁned as any of the following (21, 22): (1) patient discomfort, a sensation of a full bladder, palpable, distended bladder, with a volume of urine 400 ml; (2) any estimated postvoid residual (PVR) volume of urine greater than or equal to 200 ml per bladder scan (21); and (3) need for catheterization in 24 h.

Patients are requested to freely report the sensation of a full bladder, palpable, distended bladder at any time after the operation. The occurrence of POUR in 24 h after the operation is recorded, and POUR incidence = the number of patients who meet the diagnosis of POUR/total number of included cases in each group.

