#### Secondary Outcomes

(1)Time to first urination: the time from the end of the operation to the first urination.(2)Catheterization rate: the number of people who need catheterization in 24 h after operation in each group, catheterization rate = number of catheterization people/number of people included in each group.(3)Incidence of urinary tract infection (UTI): the occurrence of urinary tract infection during hospitalization, rate = number of infections/number of people included in each group.(4)Length of hospitalization: The average length of hospitalization of patients.(5)Adverse effects: Potential AEs may occur during the study. Patients may suffer from empyrosis, itching, allergy, dizziness with moxibustion and orthostatic hypotension, headache, dizziness, and vomiting with tamsulosin. The supervisor will manage the intervention, and any suspected AEs will be discussed with the principal investigator of the project team. If the patient shows any discomfort or changes in their condition, they are instructed to inform the investigators. The physician will provide the necessary treatment to alleviate any AEs.

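### Time to first urination is assigned a t-test or Mann-Whitney test with no rule for patients catheterized because they cannot void, who have no spontaneous voiding time or only a post-catheter one

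*Protocol article*

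**What the plan says.** The Protocol article defines the outcome under Secondary Outcomes, item 1, as "the time from the end of the operation to the first urination". It gives no rule for a patient who is catheterized before voiding.

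Catheterization is prescribed in the same terms in both arms. Treatment Group: "When the patients cannot urinate with urgent micturition desire within 24 h after the operation, catheterization will be performed". Control Group: "When the patients could not urinate with urgent micturition desire within 24 h after the operation, catheterization will be performed". It is also one of the three criteria for the primary outcome ("need for catheterization in 24 h") and a secondary outcome in its own right.

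Statistical Methods names an independent-sample t-test or a Mann-Whitney comparison, in these words: "test for intergroup comparison will be used for the time to first urination and the length of hospitalization after considering the normality and homogeneity". It summarises continuous data as mean ± SD. The only provision for absent values is general: "In FAS, for missing outcome data, multiple imputations will be used". No censoring, competing-event or worst-rank approach is named.

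**The concern.** Both named tests need one number per patient. A patient catheterized for failure to void has no spontaneous voiding time, and the reason is the very thing the outcome measures. The text leaves three routes open:

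- **Leave these patients out.** The comparison is then conditional on a post-randomization event and drops the slowest patients.
- **Treat the time as missing and impute.** Values are drawn from patients who did void, so failures receive times that are too short.
- **Use the first urination after catheter removal.** The value then depends largely on how long the catheter stayed in, and the mean and the t-test follow it.

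The trial is planned on less retention under moxibustion than under tamsulosin, so the affected group is expected to differ in size by arm. At stake is the size, and possibly the detection, of an effect on the first-listed secondary outcome.

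**Working it through.** **1. The plan's own figure.** No figure is stated for this outcome. The only stated size, 180 per group, is for the primary outcome. With the usual unpooled formula, n = (1.96 + 0.842)² × (0.281×0.719 + 0.15×0.85) / 0.131² = 7.85 × 0.3295 / 0.01716, which rounds up to 151. Then 151 × 1.2 = 181.2, rounded up to 182, close to 180. Nothing below depends on this. After the stated 20% dropout, 180 × 0.8 = 144 per arm.

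**2. How many patients could be affected.** Sample Size gives "the incidence of POUR after taking tamsulosin hydrochloride was 28.1" per cent for control and "the incidence of POUR after moxibustion therapy is 15" per cent for moxibustion. At 180 per arm that is 180 × 0.281 = 50.6 and 180 × 0.15 = 27.0 patients with retention. These are upper bounds on catheterization. Retention also counts a post-void residual of at least 200 ml, and a patient with a post-void residual has voided.

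**3. Effect of exclusion on the estimate.** Assumptions, none from the documents: log-normal latent voiding times, moxibustion median 6 h, log-SD 0.5, one catheterization threshold common to both arms, and the slowest patients catheterized.

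- Threshold: 6 × exp(0.5 × 1.036) = 10.07 h, so that 15% of the moxibustion arm exceed it.
- Control median that puts 28.1% above it: 10.07 × exp(−0.5 × 0.580) = 7.54 h.
- True median difference: 7.54 − 6.00 = 1.54 h.
- Medians among voiders only (42.5th and 35.95th latent percentiles): 6 × exp(−0.5 × 0.189) = 5.46 h and 7.54 × exp(−0.5 × 0.360) = 6.30 h.
- Apparent difference: 0.84 h, a loss of 0.70/1.54, about 45%.

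The same steps at 5% vs 10% give a threshold of 13.66 h, a control median of 7.20 h, a true difference of 1.20 h and an apparent difference of 6.76 − 5.81, about 0.94 h, a loss of about 21%.

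**4. Effect on power (simulated, same model, 144 per arm, two-sided 0.05).**

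| Catheterized (moxibustion vs control) | Mann-Whitney, catheterized left out | Mann-Whitney, catheterized ranked worst |
|---|---|---|
| 15% vs 28.1% (upper bound) | about 71% | about 96% |
| 5% vs 10% | about 70% | about 84% |

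For log-SD 0.4 to 0.6 at the upper-bound rates, exclusion gives about 69 to 72% and worst-rank about 96 to 97%.

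**5. The other two routes.** An imputation model that draws from the voiders of the same arm reproduces, on average, the voiders-only difference of step 3, because no imputed time lies beyond those already observed. With post-catheter times at the upper-bound rates, the Mann-Whitney test loses almost nothing (about 96%), because those patients still rank last. The t-test falls to about 85%; that figure also depends on the assumed catheter dwell.

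**The case against.** **The document never says that catheterized patients are excluded.** This stands. A reader might infer exclusion from the choice of tests, but the text equally allows imputation or a literal reading of first urination. On the literal reading with Mann-Whitney, almost no power is lost. The power losses in the table therefore belong to one permitted route and are not a forecast.

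**Mann-Whitney is already an option, and a scoring rule could sit in a fuller document.** This stands in part. What the article does fix is the problem: a normality-driven choice that includes the t-test, a mean ± SD summary, and blanket imputation of missing outcomes. None of these suits a time that catheterization cuts off.

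**The rates are upper bounds.** This stands. No catheterization rate is stated, and at 5% vs 10% the power gap is about 14 points, against about 25 at the upper bound.

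**A reader might infer that the result could change sign**, with moxibustion looking slower when it is not. That needs the control arm to be catheterized earlier than the moxibustion arm. The article gives both arms the same trigger and the same postoperative management. Treating staff are unblinded, so a difference in readiness is conceivable, but nothing in the text documents one.

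**Worst-rank scoring mixes timing with catheterization.** This stands. If treatment changes only whether patients void and not when voiders void, worst-rank scoring rejects in about 50% of simulated trials (150 per arm, 15% vs 28.1%), against about 5.5% among voiders only. That is a true treatment effect, but not one on timing among voiders, and it must be reported as such.

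**Conclusion.** The point holds in a limited form. The article commits to tests, a summary and an imputation rule for a voiding time that patients catheterized for failure to void do not have, or have only after catheter removal. Leaving those patients out, or imputing them from voiders, would under the assumed model shrink the median difference from 1.54 h to 0.84 h at the upper-bound rates and cost roughly 14 to 25 points of Mann-Whitney power. The direction would tend to hide a moxibustion benefit, not create one.

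The size rests on the log-normal shape, the 6 h median, the log-SD and the assumption that the slowest patients are catheterized. The expected imbalance between arms rests on the planning rates. The chi-square comparison of retention incidence, the primary outcome, is untouched. This should be corrected, but it does not threaten the trial's main conclusion.

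**What to change.** Before unblinding, state for this outcome:

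- The outcome is time to first spontaneous urination without catheterization within 24 h of the end of the operation.
- All randomized patients are kept. Catheterized patients, and those who have not voided by 24 h, are ranked as tied worst and are not imputed. Multiple imputation is kept for times missing for other reasons, such as withdrawal.
- The scoring of a patient who voids first and is catheterized later is written down explicitly.
- The comparison is the Mann-Whitney test, with medians reported. With at most 28.1% tied worst on the planning rates, the medians remain estimable. The t-test and mean ± SD are dropped for this outcome.
- The cumulative incidence of spontaneous voiding, with catheterization as a competing event, may be shown as support. It answers a related question and is not equivalent to the rank comparison.

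The cost is a change of analysis wording and one case report form item (spontaneous void or catheter, with clock time). The test is already planned and runs in the planned software. Sample size, interventions and clinical management do not change. The one downside is that the outcome then partly reflects the catheterization rate, so the two should be read side by side; that rate is already reported separately.

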### Discontinue and Data Monitoring

Patients will be dropped if they are with the following conditions: (1) With severe adverse events (AEs); (2) Unwilling to continue the study protocol. The supervisor will make a decision to discontinue if more than 25% of the patients discontinue intervention due to AEs. Case report forms (CRFs) will be used in data collection to record demographics, assessments, and reasons for patient dropout. All CRFs will be stored in a locked cabinet. At the end of the study, the investigator will submit the CRFs to the data management committee, and the investigators cannot modify the data. The data monitoring committee is independently chaired by the Statistics Teaching and Research Office of Changshu Hospital Affiliated to Nanjing University of Chinese Medicine and claims no conflict of interest. All CRFs will be preserved for at least 5 years after publication, and access to the original data of readers and reviewers is available from the corresponding author on reasonable requests.

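### Agreement between the intention-to-treat and per-protocol results is no evidence that dropout is harmless, so the planned dropout check could miss a bias

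*Protocol article*

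**What the plan says.** All references are to the protocol article. Statistical Methods plans both a full analysis set (FAS) and a per-protocol set (PPS). On missing outcomes it says: "In FAS, for missing outcome data, multiple imputations will be used". It then gives four ways of assessing dropout: a chi-square test of the rates, a comparison of reasons, and a comparison of "characteristics of dropout cases between groups, and the results using intention-to-treat and per protocol". On testing it says: "Statistical testing is two-sided, and *p* < 0.05 is considered statistically significant".

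Discontinue and Data Monitoring has patients dropped for severe adverse events or when "Unwilling to continue the study protocol". It also has reasons for dropout recorded on the case report form. Sample Size plans 180 per group with the words "Considering the dropout rate of no more than 20" per cent. Blinding states that patients know their treatment.

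The article does not define the PPS, the imputation model or the missingness assumption. It does not say whether a dropped patient's 24 h outcome is still collected. That intention-to-treat (ITT) means the FAS with multiple imputation is the natural reading, but it is not stated in terms.

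**The concern.** The article does not leave the assessment of dropout to another document; it fixes one. Of its four parts, three describe the dropouts. Only the ITT-versus-PP comparison shows what happens to the treatment effect.

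Standard multiple imputation takes a dropout to resemble the observed patients in the same arm. An analysis of completers takes the same view by leaving dropouts out. Two analyses that share an assumption cannot test it. Informative dropout is plausible here, because patients are unblinded and leave for adverse events or unwillingness. It could create a false benefit, or hide a true one, while the two results agree.

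**Working it through.** **The plan's own figure.** With 28.1% v 15%, two-sided 0.05 and power 0.8, the pooled two-proportion formula gives 154 per arm and the unpooled formula 150.7. Multiplied by 1.2 these become 185 and 181, within 3% of the stated 180. At the ceiling, 0.20 × 180 = 36 per arm are missing and 144 observed.

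**Why the two estimates agree.** Let p be an arm's true POUR rate, m the share missing and d the POUR rate among the missing.
- Completers (PP): c = (p − m·d)/(1 − m).
- Within-arm imputation (ITT): (1 − m)·c + m·c = c.
- Bias of both: p − c = m(d − p)/(1 − m).

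**Size under no true difference.** Control and moxibustion are both at p = 0.281 (Sample Size), and control dropout is uninformative. The value d = 0.50 in the moxibustion arm is an assumption, because the article gives none. SE = √[0.281 × 0.719/n + c(1 − c)/n], and the false-positive rate is P(Z > 1.96 − bias/SE) + P(Z < −1.96 − bias/SE).

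| Missing | n per arm | c | Bias | SE | False-positive rate |
|---|---|---|---|---|---|
| 5% | 171 | 0.269 | 0.05 × 0.219/0.95 = 0.012 | 0.048 | about 6% |
| 10% | 162 | 0.257 | 0.10 × 0.219/0.90 = 0.024 | 0.049 | about 8% |
| 20% | 144 | 0.226 | 0.20 × 0.219/0.80 = 0.055 | 0.051 | about 19% |

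At 20% missing and d = 0.60, the bias is 0.20 × 0.319/0.80 = 0.080 and the rate about 35%. Simulation at 20% missing (20 imputations) gave the same picture. At d = 0.50 rejection was 19.2% for PP and 19.4% for imputation, and the mean gap between the estimates was 0.03 points or less.

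**A different dropout model.** Let moxibustion patients drop out with probability 0.60 if they have POUR and 0.044 if not (20% overall). Both analyses then show about −0.14 when the truth is 0, which is as large as the planned effect of 0.281 − 0.15 = 0.131. The mean gap is 0.000, and 95% of simulated trials have a gap within about 1 point, as under random dropout. Adding a strong baseline predictor (odds ratio 4) to the imputation left the mean gap at about zero.

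**Tipping point at the planned effect.** Observed rates are 28.1% v 15%, control dropouts are at the control rate, and the test is a pooled z-test on 180 v 180.

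| Missing | Observed, control v moxibustion | Control filled in | Last significant | First not significant |
|---|---|---|---|---|
| 20% | 40/144 v 22/144, p = 0.010 | 50/180 | 12 of 36: 34/180, p = 0.046 | 13 of 36: 35/180, p = 0.063 |
| 10% | 46/162 v 24/162, p = 0.003 | 51/180 | 11 of 18: 35/180, p = 0.048 | 12 of 18: 36/180, p = 0.065 |
| 5% | 48/171 v 26/171, p = 0.004 | 51/180 | 9 of 9: 35/180, p = 0.048 | none |

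The last two rows turn on rounding. Here 162 × 0.281 = 45.5 and 9 × 0.281 = 2.5. Rounding either down puts control at 50/180. The 10% row then tips at 11 of 18, and the 5% row tips at 9 of 9 (35/180, p = 0.063 in both).

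**The case against.** **Agreement is not guaranteed.** It needs dropouts without outcomes, a PPS equal to the completers and missing-at-random imputation, and the article states none of these. The patients are inpatients with a 24 h endpoint, so someone who refuses a later session may still have a recorded outcome. In the strong scenario above, if half of the dropouts have observed outcomes, ITT gives −0.062 and PP −0.140, and significance agrees in only 42% of trials. If all do, ITT gives 0.00 and PP −0.14. A PPS that also removes deviators related to outcome opens a mean gap of about 0.02. This stands. The signal, however, comes from observed outcomes or from deviations. It says nothing about the outcomes that remain unobserved.

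**Imputation may have more to work with.** Table 1 is condensed, and symptoms, first urination or catheterization may be known before a later withdrawal. This stands in part: it could reduce bias, but it would not turn ITT-PP agreement into a test.

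**The other three parts could raise the alarm.** A reader might infer that the plan would wrongly clear a biased result. The text does not support that. It contains no rule that agreement clears a result, and reasons or characteristics could expose an imbalance. They do not show how far the effect would move, and equal dropout rates do not exclude bias: every null scenario above has equal rates in the two arms.

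**The 20% is a ceiling.** This stands, and at 5% missing the effect is small.

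**A tipping-point analysis is commonly left to the analysis plan.** True, and its absence alone would be no finding. The point is that the method the article does fix for this purpose cannot serve it.

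**Conclusion.** The concern holds in a limited form. Where dropouts lack a 24 h outcome, the PPS is essentially the completers and imputation is missing at random, agreement between ITT and PP is uninformative about outcome-related dropout, and the check could fail to detect a bias. Under the assumed 50% POUR among moxibustion dropouts, the false-positive rate runs from about 6% at 5% missing to about 19% at the ceiling. At the planned effect and the ceiling, 13 of 36 moxibustion dropouts with POUR (36%) are enough to lose significance. At 5% missing the result survives, though only just and subject to rounding.

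A reader might go further and say that the two analyses agree however informative the dropout is. The article does not support that, because it leaves open the conditions on which agreement depends. Comparing FAS with PPS is conventional and not itself an error; the weakness lies in using it to judge the impact of dropout.

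**What to change.** Keep multiple imputation as the main handling of missing outcomes, and keep the comparisons of dropout rates, reasons and characteristics as description. Keep PP as a supportive analysis, and do not use its agreement with ITT as the test of dropout impact.

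Add a tipping-point (delta-adjusted) analysis of POUR. Vary the POUR rate among patients with missing outcomes, separately in each arm, from that arm's completers' rate up to 100%. Report the combinations at which p passes 0.05, so that readers can judge whether they are plausible. Any 24 h outcome that was recorded after a patient stopped treatment should be used as observed, not varied.

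The cost is a few lines of text and a short extra analysis, with no new data or patients. The change should be made before unblinding. The downside is that the result may look less robust.

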### Oversight and Monitoring

The Office of Academic Research in our hospital will supervise and monitor the trial independently and audit the trial twice a year. If any changes are needed to the protocol, we will first notify the sponsor. After making the revised protocol, we will update it on the registry site.

## Discussion

Many risk factors in anorectal surgery, such as anesthesia, surgical stimulation, or pain, can easily cause spasms of the bladder neck and urethral sphincter or weak contraction of the bladder detrusor, inducing reflex dysuria and a high incidence of POUR. POUR is a common urological emergency, which occurs 6–8 h after hemorrhoidectomy, manifested with urgency, lower abdominal pain, distress, refusal to press, and bladder enlargement. Therefore, how to effectively prevent POUR after hemorrhoidectomy is important.

Tamsulosin hydrochloride is a superselective *α*-1a receptor blocker, and it could block *α*1a adrenergic receptors in the prostate and relax the smooth muscle of the prostate, thus improving dysuria and other symptoms. The incidence of postural hypotension is relatively low due to the high selectivity of this drug. It can not only effectively treat urinary retention, and could also reduce the incidence of POUR (23, 24), yet with certain side effects, including dizziness, headache, syncope, and retrograde ejaculation (25).

In China, moxibustion is a commonly used therapy for urinary retention. Moxibustion is an external treatment based on TCM theory. By baking acupoints with burning moxa wool, it is characterized by simple operation, painless, fewer side effects, and stable efficacy. It has been used for more than 2,500 years, and it could dredge meridians and regulate qi-blood to prevent and cure diseases according to TCM theory. By burning moxa without flame over the acupoints, patients will get a warm feeling when close to the body. Its thermal effects, radiation effects, and pharmacological actions (26) could function as an analgesic, alleviating inflammation and enhancing immunity.

Clinical studies have proved that moxibustion could effectively improve urination disorder (27–29), yet there are few highly designed clinical trials to prove its effects in preventing POUR in hemorrhoidectomy. Therefore, we designed a randomized controlled clinical study to compare the difference of prophylactic moxibustion with tamsulosin in reducing the incidence of POUR against patients of hemorrhoidectomy in 24 h and to clarify the efficacy of moxibustion to prevent POUR.

A double-blinded, placebo-controlled trial is supposed to be more applicable to assess the therapeutic effect of prophylactic moxibustion in reducing POUR, but it is difficult to carry out sham moxibustion because of the nature of the moxibustion procedure. Heat is supposed to be the most important factor of moxibustion, and the warm stimulation of moxibustion could be easily distinguished from sham moxibusiton. Although there are several reports about sham moxibustion devices used in clinical trials (30–32), it cannot fully be achieved. Thus, double-blinding and placebo control will not be involved in this study. However, many Chinese patients are awaiting to have a positive effect on moxibustion, despite the magnitude of the effect. It made the placebo effect an inseparable part of moxibustion efficacy. It has been previously discussed that there might be placebo effects involved in intervention with moxibusion (30, 31). When analyzing the results, the placebo effect should be taken into consideration in our study.

In addition, there are still several other limitations in this study. First, our study is single-centered, which may affect the conclusions. Second, many studies reported that the dosage of tamsulosin is higher with 0.4 mg (33, 34) or 0.8 mg (35). We used 0.2 mg tamsulosin according to the instruction in this study, and it might influence the effect.

